#### Data analysis of the effect evaluation

The effectiveness of SMS will be assessed by intention-to-treat analyses. The comparability of patients in the intervention and control groups regarding baseline characteristics and demographics will be described and tested for significant differences (t-tests and Chi-square tests). The average changes in DFT score will be calculated, as well as the number of patients that have DFT ≤4 after receiving SMS (T4 and T12). Separate scores will be calculated for the subscales of the secondary outcome measures. Changes in the primary and secondary outcomes between the intervention and control groups will be analysed using multilevel analyses (linear and logistic regression methods) as this will account for intracluster correlation among PNs. Multivariate regression analyses will be used to adjust the results for co-variables such as patient characteristics (age, sex, socio-economic status) and PN characteristics (age, educational background).

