##### Detection procedure

The diagnostic procedure that was used to recruit patients for the study to evaluate the original MPI is not feasible in routine primary care: it was limited to depression, and included an extensive and time-consuming diagnostic interview (the Mini International Neuropsychiatry Interview) to confirm a diagnosis of depression according to psychiatric criteria. For SMS, PNs will have to decide during routine diabetes check-ups whether watchful waiting, offering psychosocial self-management support or a referral to the GP because of symptoms of mental health problems is most appropriate. Therefore, we have introduced a stepped approach that allows interventions not sooner or more intense than necessary and not later or less intense than required. The approach is as follows. During each regular diabetes check-up, PNs will explore whether the patient is experiencing problems in daily life. Then they verbally administer the ‘Daily Functioning Thermometer’ (DFT), a visual analogue scale to rate the overall burden of diabetes. (See the Measurements section below for more information about the instruments.) Practice nurses will also verbally administer the 3-item Distress Screener (DS), a quick-scan instrument for emotional distress and an indicator of potential underlying severe mental health problems [22]. Patients with DS > 3 will be asked to complete the Four-Dimensional Symptom Questionnaire (4DSQ) [23] immediately after the consultation. This self-report measure is widely used in Dutch primary care to distinguish non-specific general distress from depression, anxiety and somatisation. Scoring the 50 items of the 4DSQ should take 5–10 minutes The completed 4DSQ will be returned to the PN, who will score the 4DSQ using a scoring form. Patient’s scores on the 4DSQ will distinguish between mild, moderate and severe mental health problems. Patients who experience problems of daily functioning (DFT > 4) and emotional health problems (DS > 3 combined with moderate scores on subscales of the 4DSQ) will receive self-management support from the PN. If a patient has only ‘mild’ scores on the 4DSQ, the PNs will opt for watchful waiting. The same option will be used for patients with moderate scores on the 4DSQ who do not report problems of daily functioning due to diabetes (DFT ≤ 4). These patients will be informed by telephone that there is as yet no indication for extra consultations. Patients with a ‘severe’ score on at least one of the subscales will be referred to the GP. The detection protocol is summarised in Table 2.

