#### Measurements

To assess the effectiveness of SMS, follow-up measurements will be carried out at baseline and 4 and 12 months after inclusion. Table 3 provides an overview of the measures of the effect evaluation and the times of assessment.

**Table 3 T3:** Effect evaluation: outcome measures and time of assessment

**Concept**	**Measurement**	**Items**	**Moment in time**			
			**3-monthly diabetes consultations during follow-up**	**T0**	**T-4**	**T-12**
*Primary outcome*						
Daily functioning	DFT	1		*	*	***
*Secondary outcomes*						
Diabetes-related emotional distress	PAID	20		*	*	***
Mental health problems	PSYCHLOPS	9	*^2^	*^1^	*	***
	4DSQ	50			*	*
Quality of life	SF-12	12		*	*	***
Participation and autonomy	IPA	32 + 9		*	*	***
Job performance	SF-HLQ	5		*	*	*
Self-management knowledge and behaviour	PIH-NL	12		*	*	***
General self-efficacy	GSES-12	12		*	*	*
Control over the disease	Average blood glucose level (HbA1c)	1	*			
Health care use		5		*	*	*
*Covariates*						
Patient demographics	Sex	1		*		
	Age	1		*		
	Year of diagnosis	1		*		
	Treatment of diabetes	1		*		
	Marital status	1		*		
	Education	1		*		
Practice nurse demographics	Age	1		*		
	Training	1		*		
	Type of general practice(s) (one GP, two GPs, group, health centre)	1		*		

1 Only patients in intervention arm. Risk of contamination.

2 Only eligible patients (Distress Screener > 3).

* = measuring moment.

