##### Secondary outcome measures

Three instruments will assess patients’ emotional health status.

Diabetes-related emotional distress will be measured by means of the Problem Areas in Diabetes questionnaire (PAID). This 20-item scale (with five-point Likert scales) describes common problematic situations for diabetes patients, each representing a unique area of diabetes-specific emotional distress. The sum of the scores for the 20 items is multiplied by 1.25 to get a final score between 0 and 100. The Dutch PAID has good internal consistency and validity [35-37].

The Four-Dimensional Symptom Questionnaire (4DSQ) will be used to measure the presence and severity of mental health problems [23]. The levels of distress (16 items), depression (6 items), anxiety (12 items) and somatisation (16 items) will be assessed. The reference period is ‘the past week’. The item scores are summated to obtain scale scores. The 4DSQ has been found to be a valid self-reported questionnaire in the primary care setting [23]. For a more qualitative evaluation of emotional problems that patients experience, we will use the Psychological Outcome Profiles (PSYCHLOPS). The PSYCHLOPS asks patients to describe and score their own emotional health problems. It is a validated patient-generated measure with pre-therapy, during-therapy and post-therapy versions. The instrument is intended to measure individual changes. It is responsive to change and is internally consistent [38].

Both PSYCHLOPS and 4DSQ explicitly expect patients to define and rate their emotional health problems. An increased awareness about their emotional problems of daily functioning could influence the issues discussed during the diabetes consultation, which could result in reduced contrast between the two groups. We will not use the 4DSQ and the PSYCHLOPS in the control group at T0, as the timing of the baseline measurement is just before a diabetes consultation, whereas the assessment at T4 is further removed from a diabetes consultation. Inclusion of the PSYCHLOPS and 4DSQ at both T4 and at the end of the follow-up period (T12) will provide insight into individual changes. In the intervention group, inclusion of the PSYCHLOPS at baseline will provide valuable information about the patients’ individual emotional problems. The 4DSQ does not need to be included in the baseline measurement as it is already part of the SMS intervention.

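### The planned between-arm analysis of changes cannot be run from baseline for 4DSQ and PSYCHLOPS, which have no control-arm T0 measurement

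*Protocol article*

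**What the plan says.** All places are in the protocol article.

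- **Data analysis of the effect evaluation:** "Changes in the primary and secondary outcomes between the intervention and control groups will be analysed using multilevel analyses". The methods are linear and logistic regression. No secondary outcome is exempted.
- **Secondary outcome measures:** "We will not use the 4DSQ and the PSYCHLOPS in the control group at T0". The reason given is that asking patients to define and rate emotional problems could influence the coming consultation and so reduce contrast; "the timing of the baseline measurement is just before a diabetes consultation".
- **Same section, intervention arm:** "The 4DSQ does not need to be included in the baseline measurement as it is already part of the SMS intervention".
- **Same section, follow-up:** "Inclusion of the PSYCHLOPS and 4DSQ at both T4 and at the end of the follow-up period (T12) will provide insight into individual changes".
- **Table 3 (Measurements):** 4DSQ is marked at T4 and T12 only. PSYCHLOPS is marked at T0, T4 and T12, with a footnote to the T0 mark: "1 Only patients in intervention arm. Risk of contamination".
- **Timing (Measurements):** "follow-up measurements will be carried out at baseline and 4 and 12 months after inclusion".

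**The concern.** The analysis rule and the measurement schedule do not fit together for two of the three instruments chosen to assess emotional health status, which is part of research question 2. Whoever follows the analysis sentence literally has to find some other change to compare, and only T4 to T12 exists in both arms.

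T0 falls just before a check-up, and intervention nurses apply the detection steps at each 3-monthly check-up. T4 therefore normally comes after exposure to SMS has begun. A change that starts at T4 starts from a value the intervention may already have altered, so it is not a substitute for a change from baseline. If the choice between follow-up scores and T4-to-T12 change stays open until the data are seen, the two can give opposite answers.

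**Working it through.** **1. What can be computed**

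| Instrument | T0 intervention | T0 control | T4 and T12, both arms | Change from T0 between arms |
|---|---|---|---|---|
| 4DSQ | no | no | yes | not computable |
| PSYCHLOPS | yes | no | yes | not computable |
| PAID | yes | yes | yes | computable |
| DFT (primary) | yes | yes | yes | computable |

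The 4DSQ completed around the consultation does not fill the gap. Under Detection procedure it goes only to patients scoring above 3 on the Distress Screener at that visit, and it has no control counterpart because control nurses give usual care.

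**2. What a T4-to-T12 contrast would estimate**

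Let e(t) be the control mean minus the intervention mean at time t, on a scale where lower is better, so that a positive value is benefit.

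- Change from T0: e(12) − e(0). Randomisation makes e(0) zero in expectation, so this estimates e(12).
- Change from T4: e(12) − e(4).

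With e(4) = e(12) = d, the second contrast is 0. With e(4) = d and e(12) = d/2, it is −d/2. With e(4) = 0 and e(12) = d, it is d and nothing is lost. This algebra needs no assumption about effect size.

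**3. Illustration of size**

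The plan gives no figure for these instruments, so its sample size for the primary outcome is used. That figure reproduces closely. For 20% against 5%, two-sided alpha 0.05 (sidedness assumed) and power 0.90 (printed as beta), 101 per arm are needed. The design effect with 5 patients per nurse and ICC 0.04 is 1 + (5 − 1) × 0.04 = 1.16, and 101 × 1.16 = 117.2, against the stated 116. The effective number per arm is 116 / 1.16 = 100.

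Assumptions that are not in the documents: a full effect of 0.4 SD; a T4–T12 correlation ρ of 0.5 to 0.7; the same design effect for scores and for changes. In SD units:

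- SE of a difference in scores = √(2/100) = 0.141.
- SE of a difference in change = √(2(1 − ρ)) × √(2/100) = 0.141 at ρ = 0.5 and 0.110 at ρ = 0.7.

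| Effect at T4, T12 | T4-to-T12 contrast | Probability of rejection, change (ρ = 0.5; 0.7) | Power, T12 scores |
|---|---|---|---|
| 0.4, 0.4 | 0.0 | 0.05; 0.05 | 0.807 |
| 0.4, 0.2 | −0.2 (wrong sign) | 0.293; 0.447 | 0.293 |
| 0.2, 0.4 | 0.2 | 0.293; 0.447 | 0.807 |
| 0, 0.4 | 0.4 | 0.807; 0.955 | 0.807 |

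In the second row the T4 comparison of scores has power 0.807. In the last row the change contrast does at least as well as the scores.

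**The case against.** **The word may be loose.** The same paragraph counts patients at or below the DFT cut-off at T4 and T12, which is a follow-up status and not a change. A comparison of 4DSQ and PSYCHLOPS scores could be meant, and model details for each outcome commonly sit in an analysis plan that is not shown. This stands in part and lowers the weight of the point. It does not remove it, because the article states a rule that its own schedule cannot meet for two instruments.

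**Stronger readings that the documents do not support:**

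- A reader might infer that T4-to-T12 change is the planned effect estimate. No section says so. The T4 and T12 measurements are offered as insight into change within individuals, after PSYCHLOPS has been introduced as a more qualitative evaluation. Nor does that sentence attribute such change to SMS.
- A reader might infer that a real effect would be hidden in any case. Only the part reached by T4 cancels. Detection recurs at every check-up, and the Discussion expects that some recruited patients will not be detected or treated, so some support may start after T4.
- A reader might suspect that PSYCHLOPS change in the intervention arm alone will be presented as an effect, with regression to the mean mistaken for benefit. The stated purpose of that T0 measurement is information about patients' individual problems, which is descriptive.
- A reader might call the missing control baseline itself a fault. It is disclosed and reasoned. The fault lies only in the analysis text, which was not adapted to it.

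**Conclusion.** The inconsistency is established from the text: a between-arm change from baseline is planned for all secondary outcomes and is not computable for 4DSQ or PSYCHLOPS. The consequence is conditional. If T4-to-T12 change were used instead, it would subtract whatever effect had been reached by T4. In the illustration, a maintained 0.4 SD effect would be detected only at the 5% error rate, against about 81% power for T12 scores. Those probabilities rest on the assumed effect size, correlation and design effect; the zero and the sign reversal do not.

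The weight is moderate. Two secondary instruments are affected. The primary DFT, and PAID as the third emotional-health instrument, have T0 in both arms. No data are lost. Comparing follow-up scores without a baseline is valid because nurses are randomised, provided that patients are recruited in the same way in both arms, as the central postal screening intends.

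**What to change.** Under Data analysis of the effect evaluation:

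1. Exempt 4DSQ and PSYCHLOPS from the analysis of changes. Compare their T4 and T12 scores between arms in the multilevel model, adjusted for measures taken in both arms before the consultation: T0 PAID, T0 SF-12 mental component and the screening Distress Screener score.
2. For PSYCHLOPS, restrict this comparison to items scored the same way in both arms. It is patient-generated and has separate versions for before, during and after therapy.
3. State that within-person T4-to-T12 change, the intervention-arm T0 PSYCHLOPS and the consultation 4DSQ are descriptive only, and add the same clarification under Secondary outcome measures.

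The control-arm measurement schedule need not change. The cost is a few sentences in the protocol and analysis plan, fixed before outcome data are examined. All the data are already due to be collected.

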### Clinical effect evaluation

#### Design

The effect evaluation of SMS involves a pragmatic 2-armed cluster-randomised controlled trial (cluster-RCT) with PNs as the unit of randomisation. Allocation concealment will be achieved by having an independent experienced research assistant perform a blockwise randomisation using a random number seed computer program. PNs (n = 46) will be assigned to an intervention group or control group at an allocation ratio of 1:1, after stratification into PNs working alone in a practice, PNs working in a team and PNs working in different practices. PNs working in the same general practice will be randomised to the same trial arm.

PNs in the intervention arm will be trained to apply SMS in addition to the usual care, which consists of 3-monthly diabetes check-ups according to the current guidelines [10]. PNs in the control arm will be instructed to provide usual care.

Patients with emotional distress and problems of daily functioning will be included in the effect evaluation. To maintain the balance between the intervention and control groups, a screening procedure will be carried out by the research centre. A self-administered postal questionnaire will be used to detect eligible patients.

Approval for this study has been obtained from the Medical Ethics Committee of Maastricht University/University Hospital Maastricht.

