#### Sample size calculation

Assuming an alpha of 0.05 and a beta of 0.90, an improvement in perceived daily functioning (defined as a score less than or equal to 4 on the Daily Functioning Thermometer (DFT), our primary outcome) at T12 occurring in 20% of the patients in the intervention group versus 5% of those in the control group requires at least a net number of 116 patients per arm (N = 232; 5 patients per practice nurse). It will be necessary to take account of a possible dependence between observations on patients of the same practice nurse. The intra-class correlation coefficient (ICC) is assumed to be 0.04, a median value for cluster-RCTs in the primary care setting [33]. Assuming a 30% loss to follow-up [17] we need to recruit at least 331 patients (8 per PN). Since participation in the screening procedure will not necessarily mean that patients also give informed consent for the effect evaluation, 10 consecutive patients for each PN will be invited to participate in the effect evaluation (N = 460).

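### The effect analysis names neither the T0 value of the outcome nor the randomisation stratum as a covariate; naming both would be a low-cost gain in precision

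*Protocol article*

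**What the plan says.** Under Data analysis of the effect evaluation, the Protocol article gives the primary outcome in two forms. One is continuous: "The average changes in DFT score will be calculated". The other is the number of patients at or below the cut-off of 4 at T4 and T12. Changes in primary and secondary outcomes are compared between arms by multilevel linear and logistic regression, with practice nurse (PN) as the cluster. Further regression will "adjust the results for co-variables such as patient characteristics (age, sex, socio-economic status) and PN characteristics (age, educational background").

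The Design section of the clinical effect evaluation says that PNs are randomised "after stratification into PNs working alone in a practice, PNs working in a team and PNs working in different practices". This factor appears neither among the named covariates nor in the covariate block of Table 3. Practice type (Table 3) and the number of diabetes PNs per practice (Background variables) are recorded. They are related to the stratum but are not the same variable.

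Table 3 marks the DFT at T0, T4 and T12. Baseline comparability is to be "described and tested for significant differences (t-tests and Chi-square tests").

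The sample size rests on the binary form, "defined as a score less than or equal to 4 on the Daily Functioning Thermometer (DFT), our primary outcome", at T12.

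**The concern.** The article is not silent on adjustment. It names five covariates, none of which is likely to predict follow-up DFT as well as T0 DFT does. It also leaves out the one factor that the randomisation was built around.

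Two things are at stake for the continuous outcomes. First, an analysis of change without T0 in the model fixes the slope of follow-up on baseline at 1. When the true slope is below 1, precision is lost. Second, at most 46 PNs are randomised, and there are fewer independent units because PNs who share a practice go to the same arm. Some chance difference in T0 between arms is therefore to be expected, and a change score over-corrects for it. Patients are also selected on DFT > 4, so regression to the mean is likely and a slope below 1 is plausible.

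**Working it through.** **1. The plan's own figure.** The inputs come from Sample size calculation: "Assuming an alpha of 0.05 and a beta of 0.90" (0.90 read as power; two-sided assumed), "occurring in 20% of the patients in the intervention group versus 5% of those in the control group", ICC 0.04 and 5 patients per PN.

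- Pooled two-proportion formula: n = [1.960·√(2 × 0.125 × 0.875) + 1.282·√(0.20 × 0.80 + 0.05 × 0.95)]² / 0.15² = (0.917 + 0.584)² / 0.0225 ≈ 100.1 per arm, or 101 rounded up.
- Design effect: 1 + (5 − 1) × 0.04 = 1.16. Then 100.1 × 1.16 ≈ 116 (117 if 101 is carried forward).
- The article "requires at least a net number of 116 patients per arm (N = 232; 5 patients per practice nurse"), so its figure is reproduced. Power at 116/1.16 = 100 effective patients per arm is 0.900.
- Loss to follow-up: 232/0.70 = 331.4, against 331 stated.

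This calculation uses no baseline value. Adding or omitting T0 does not alter it.

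**2. Change score against T0-adjusted model, continuous outcomes.** Let s0 and s1 be the SDs at T0 and follow-up, and r their correlation.

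- Change-score variance: s0² + s1² − 2r·s0·s1.
- T0-adjusted variance: s1²(1 − r²).
- Difference: (s0 − r·s1)², which is never negative.

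With s0 = s1, the ratio of adjusted to change-score variance is (1 − r²)/[2(1 − r)] = (1 + r)/2. The last column is Φ[3.242·√((1 + r)/2) − 1.960]. The article gives no r, so a range is shown.

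| Assumed r | Adjusted / change-score variance | Extra patients for change score | Change-score power where adjusted power is 90% |
|---|---|---|---|
| 0.3 | 65% | 54% | 74% |
| 0.5 | 75% | 33% | 80% |
| 0.7 | 85% | 18% | 85% |

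**3. Chance imbalance.** With equal SDs, a T0 difference of d SD shifts the change-score estimate by (r − 1)d. For d = 0.2, the shift is 0.14, 0.10 or 0.06 SD in absolute size at r = 0.3, 0.5 or 0.7.

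To judge what d is likely, take 331 patients, 8 per PN and ICC 0.04, so the design effect is 1 + 7 × 0.04 = 1.28. The SD of the T0 difference is √(2 × 1.28/165.5) ≈ 0.12 SD, and its mean absolute size is about 0.8 × 0.12 ≈ 0.10 SD. The typical shift at r = 0.5 to 0.7 is then 0.05 to 0.03 SD.

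**4. Baseline tests.** If the same ICC of 0.04 applied to a baseline variable, a t-test that ignores clustering would have a false-positive rate of 2[1 − Φ(1.96/√1.28)] ≈ 8.3%. The article does not link these tests to the choice of covariates.

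**5. Where T0 adjustment is possible.** Table 3 marks T0 for the DFT, PAID, SF-12, IPA, SF-HLQ, PIH-NL, GSES-12 and health care use. It gives the 4DSQ no T0 mark and restricts T0 PSYCHLOPS to the intervention arm. HbA1c is marked only at the 3-monthly consultations.

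**The case against.** The strongest reply is that the list of covariates is introduced by example and so stays open, and that a statistical analysis plan may add T0 and the stratum. A reader might infer that the plan excludes both. It does not: it fails to name them. That lowers the weight of the point. It does not remove it, because the article does choose covariates and the ones it chooses are the less useful ones.

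It is also fair to say that a change-score model is not established. Logistic regression cannot take a change score as its outcome, so *changes* may describe a repeated-measures model, and the average change may be purely descriptive. The efficiency loss in the table is therefore conditional on the change-score reading.

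A reader might infer that the primary comparison is underpowered without T0. The documents do not support this. Such a figure can be produced by assuming that a quarter of patients score above 4 and that r is 0.6 to 0.8. The control responder rate among selected patients then becomes about 32% to 46%, and a 15-point gain has roughly 57% to 59% power at 100 effective patients per arm. But that replaces the protocol's 5% control rate. At 20% versus 5%, power is 90% with no covariates.

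Two further inferences go too far. The imbalance in step 3 averages to zero over randomisations, so it is chance error and not systematic bias. Leaving out a stratification factor usually makes standard errors somewhat too large, so it does not invalidate the test.

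Finally, the gain for DFT depends on whether T0 is a reading separate from the screening DFT. Screening goes out six weeks before the consultation and baseline is described as just before one, which suggests two readings. If T0 is the screening reading itself, selection narrows its spread. In simulations under the same assumptions, the gain over a change score was then only about 0 to 3 power points.

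**Conclusion.** The point holds as an avoidable loss of precision, not as an error that undermines the trial. The named covariates omit the T0 outcome and the randomisation stratum. If the linear analyses are change scores, T0 adjustment would cut the variance to 75% to 85% of its change-score value at r = 0.5 to 0.7. It would also remove a chance shift of typically 0.03 to 0.05 SD. Both figures assume equal variances and a value of r that the article does not give.

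For the powered endpoint, every patient is above 4 at screening, so the dichotomised baseline carries almost no information. Continuous T0 DFT can help, since patients just above the cut-off and those far above it differ in their chance of reaching 4. The size of that help cannot be derived from the article. The 116 per arm and 90% power are untouched. The effect of omitting the stratum tends towards conservatism and cannot be quantified here. The baseline significance tests change no effect estimate.

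**What to change.** In Data analysis of the effect evaluation, state that:

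- each multilevel model takes the follow-up value (T4, T12) as its outcome, not the change;
- each model includes as fixed effects the T0 value of that outcome where it is measured in both arms, and the three-level PN stratum, in addition to the covariates already listed;
- the logistic model for DFT ≤ 4 uses continuous T0 DFT;
- 4DSQ and PSYCHLOPS are analysed without T0 adjustment, because controls have no T0 value;
- HbA1c is adjusted only if a pre-intervention value is available from the registration system.

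Optionally, present baseline comparability descriptively and drop the t-tests and chi-square tests.

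The cost is wording. The T0 values concerned are already scheduled in Table 3, and the stratum is known from the randomisation. The sample size does not change.
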